## Abstract

**Background:**

Self-harm in young people is a growing concern and reducing rates a global priority. Rates of self-harm documented in general practice have been increasing for young people in the UK in the last two decades, especially in 13–16-year-olds. General practitioners (GPs) can intervene early after self-harm but there are no effective treatments presently available. We developed the GP-led COPING intervention, in partnership with young people with lived experience and GPs, to be delivered to young people 16–25 years across two consultations. This study aims to examine the feasibility and acceptability of conducting a fully powered effectiveness trial of the COPING intervention in NHS general practice.

**Methods:**

This will be a mixed-methods external non-randomised before-after single arm feasibility study in NHS general practices in the West Midlands, England. Patients aged 16–25 years who have self-harmed in the last 12 months will be eligible to receive COPING. Feasibility outcomes will be recruitment rates, intervention delivery, retention rates, and completion of follow-up outcome measures. All participants will receive COPING with a target sample of 31 with final follow-up data collection at six months from baseline. Clinical data such as self-harm repetition will be collected. A nested qualitative study and national survey of GPs will explore COPING acceptability, deliverability, implementation, and likelihood of contamination.

**Discussion:**

Brief GP-led interventions for young people after self-harm are needed to address national guideline and policy recommendations. This study of the COPING intervention will assess whether a main trial is feasible.

**Registration:**

ISRCTN (ISRCTN16572400; 28.11.2023).

^. To address this intervention evidence gap, we developed using a combination complex intervention development approach (evidence and theory approach and a partnership approach with young people with lived experience of self-harm and GPs) a brief GP-led psychosocial intervention (COPING) to help young people aged 16–25 years, across two GP consultations, avoid future self-harm (COPING-ID study, IRAS 294180).

Through early intervention in general practice there is potential to prevent long-term self-harm in young people, reduce NHS self-harm treatment costs, and future mental health and specialist (emergency, paediatric, medical) care costs. If the COPING intervention is feasible and acceptable, a future main randomised controlled trial (RCT) has the potential to bring substantial benefit to patients and the NHS. This feasibility study aims to examine aspects of the feasibility of future pragmatic RCT to assess the effectiveness of COPING in the NHS and inform its design.

### Objectives

To examine aspects of the feasibility of a fully powered RCT of the COPING intervention across the areas of recruitment, delivery, and retention and follow-up. Specific objectives are:

i) Estimate participant consent and willingness of enrolled participants and GPs to be randomised in a future RCTii) Assess GP fidelity to COPING delivery and participant adherence to COPINGiii) Examine completeness of participant follow-up data collectioniv) Explore the acceptability of COPING for both participants and GPs, and deliverability of COPING for GPs

## Methods

### Study design

This study is a mixed-methods external non-randomised before-after single arm feasibility study.

This study is registered on ISRCTN registry, 28.11.2023: ISRCTN16572400;
https://www.isrctn.com/ISRCTN16572400.

### Study setting

NHS general practices in the West Midlands, England.

### Eligibility criteria

Patients will be eligible to participate if they are aged 16–25 years and have self-harmed (according to the definition of the National Institute for Health and Care Excellence) in the last 12 months
^
1
^. Exclusion criteria include acute risk of suicide or harm to others necessitating urgent referral/admission; moderate to severe learning disabilities; current psychotic episode or organic mental illness; receiving current psychological therapy; patient inappropriate for COPING at clinician discretion; and lacking capacity for informed consent.

At general practice study sites, GPs will be eligible to deliver COPING if they complete the site COPING training.

### Intervention

All participants will receive the COPING intervention delivered by GPs to young people aged 16–25 years after self-harm across two GP appointments. COPING’s development was guided by the new Medical Research Council’s (MRC) framework for developing and evaluating complex interventions
^
19
^. COPING was developed through a ‘combination’ development approach (O’Cathain’s taxonomy - integrating both theory and evidence-based and partnership approaches)
^
20
^. It was informed by the Behaviour Change Wheel, and included coproduction and prototyping (Hawkin’s framework) in its design and refinement
^
21,
22
^.

COPING comprises eight behaviour change techniques (BCTs) aimed at influencing the selected target behaviours for the young person and the GP. The target behaviours are: i) the young person using new skills to avoid self-harm and ii) encouraging GP use of COPING in usual NHS practice. The BCTs are problem solving, self-monitoring of behaviour, goal setting behaviour, review behaviour goal, social support (practical), instruction on how to perform the behaviour, demonstration of the behaviour, and rewarding completion. In the first COPING appointment the GP and participant agree on new skills aligned to the function of the self-harm to use when urges of self-harm occur, and a diary is provided. In the second appointment the GP reviews progress with the participant. The first appointment will be in-person and the format and time (from two to four weeks) of the second COPING appointment will be decided between the GP and participant.

The COPING training will be delivered by the Chief Investigator (CI) to site GPs in person and last up to 60 minutes. The training will include presenting the study background (including COPING-ID), rationale and aim, providing the COPING intervention materials, offering to show an example COPING delivery video, and highlighting study procedures and safety reporting.

### Outcomes

The primary outcomes are:

- Consent to study of eligible patients- Young people participants willing to be randomised in a main RCT- Fidelity to COPING- Participant adherence to COPING- Participant follow-up rate of outcome measures- Acceptability of COPING to participants and GPs- Deliverability of COPING

The secondary outcomes are:

- Response rates of invited practices to participate- Identification of patients at sites- Proportion of identified patients eligible for study inclusion- Participant recruitment uptake through recruitment strategies- Willingness of GPs to be randomised in a main RCT- Assessment of outcome measure to use as the primary outcome in a main RCT- Proportion of participants with repetition of self-harm- Participant attrition, follow-up, and withdrawal rates

This feasibility study is not designed to evaluate health outcome measures formally. We will collect clinical effectiveness data that may support the justification for a future main trial. These data may also be used to decide which outcomes could and should be collected in a future RCT, and to estimate parameters required to calculate the sample size calculation for a fully powered RCT.

The progression decision-making process will include consideration of the feasibility study progression outcomes (aligned to the primary outcomes: see
Table 1) with the study steering committee (SSC), patient and public involvement (PPI) group, and research team to consider if moving to a fully powered RCT is feasible.

**Table 1. T1:** Progression criteria for a future main trial.

Criteria	Go – proceed to RCT	Amend – proceed with minor changes	Stop – do not proceed unless major changes are possible
Consent to study in eligible patients	>30%	15–30%	<15%
Young people participants willing to be randomised in a future RCT	>85%	60–85%	<60%
Fidelity to COPING treatment checklist	>67%	40–67%	<40%
Participant adherence to COPING	>67%	40–67%	<40%
Participant follow-up rate of outcome measures	>80%	50–80%	<50%
Acceptability of COPING to GPs and patients	COPING judged very acceptable by GPs and patients by qualitative data	COPING judged acceptable by GPs and patients by qualitative data	COPING judged somewhat acceptable by GPs and patients by qualitative data
Delivery of COPING by GPs	Delivery of COPING judged strongly feasible by qualitative data	Delivery of COPING judged feasible by qualitative data	Delivery of COPING judged possibly feasible by qualitative data

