### Sample size

Non-randomised COPING delivery:

We will aim to recruit approximately six general practice sites and around 3 GPs at each site. The incidence rate of recorded self-harm in young people in general practice is around 60 per 10,000 person-years
^
23
^. This equates to 60 per 1,000 for the 16–25 age group over one year. If half are eligible for the study (30 per 1,000) and two-thirds of those are identified by our recruiting methods (20 per 1,000) then in a typical GP practice (assumed 6,000 registered patients of which 900 (15%) are in the 16–25 age group) about 18 eligible young people will contact their GP practice per year after self-harm (1.5 eligible young people per practice per month). If six practices are recruited to take part, nine young people would be expected to be eligible per month, and around 104 (the target eligible population size) over about 12 months. From this number (n=104) we would expect to recruit 31 participants (30%) (fulfilling the Go signal for progression for the recruitment criterion – see
Table 1) into the study.

The sample size of n=31 participants is required to test against the feasibility progression criteria (specifically the cut-off for a STOP signal) with at least 90% power, using the normal approximation method for binary outcomes using a 1-sample 1-sided test with 5% alpha (type I error) using the approach of Lewis
*et al.*
^
24
^ In line with the recommendation of the CONSORT-extension for randomised pilot and feasibility studies this provides necessary justification for the sample size requirement for the evaluation of the progression criteria for this feasibility study
^
25
^.

GP survey:

A sample of 100 GPs across England will be surveyed to elicit GP views about a future main RCT of COPING. Achieving 100 GP responses from a convenience sample has recently been shown to be achievable
^
26

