### Recruitment

General practices in the National Institute for Health and Care Research Local Clinical Research Network (CRN) West Midlands will be invited to participate in the study by email. Practices who agree to participate will receive a local information pack, a site initiation visit, COPING training, and an investigator site file. Recruited practices therefore become study sites. Each site will have a designated principal investigator (PI), and each site PI will identify GPs who want to deliver COPING to participants. GPs who use COPING with participants become study co-investigators

Patient recruitment to self-harm clinical trials in NHS general practice is untested and thus we will test three participant recruitment strategies which have been informed by the study’s PPI group:

1) General practice electronic healthcare records: practice database searches will be developed for sites to use to identify potentially eligible patients.2) Study advertisement: recruitment posters will be displayed in site waiting rooms, linked community pharmacies, and nearby educational institutions to share the study opportunity.3) Routine clinical practice: members of the clinical team can signpost potentially eligible patients to the study opportunity during routine consultations.

In strategy one, potential eligible patients will be identified at research sites through searching practice-based electronic healthcare registers using a standardised strategy. A practice clinician will screen the identified list of potentially eligible patients and exclude those ineligible. The remaining eligible patients, with a prior telephone check where appropriate, will be sent a text message and postal invitation from the practice signposting them to the study webpage, where the participant information sheet (PIS) and e-consent form can be found. A reminder will be sent after two weeks if no response. A simplified two-page PIS summarising what will be required from participants enrolled in the study will be made available on the study website.

Other potentially eligible patients may also be approached opportunistically by a member of the clinical care team in routine practice (strategy three). These patients and those who see the study advertised in the community around participating sites (strategy two) will be able to scan the study QR code to complete an online expression of interest. If deemed eligible for the study, they will be invited to consent into the study.

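### Table 1 has no criterion for recruitment volume: its recruitment row is a consent ratio that can read Go when yield per practice is far below plan

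*Protocol article*

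**What the plan says.** Recruitment is a declared feasibility question. The abstract states: "Feasibility outcomes will be recruitment rates, intervention delivery, retention rates, and completion of follow-up outcome measures". The Objectives section sets out to examine feasibility "across the areas of recruitment, delivery, and retention and follow-up". The Recruitment section gives the reason for trying several routes: "Patient recruitment to self-harm clinical trials in NHS general practice is untested and thus we will test three participant recruitment strategies".

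Under Outcomes, the decision on a main trial is to consider the "feasibility study progression outcomes (aligned to the primary outcomes: see" Table 1). Table 1 has seven rows. The one on recruitment is "Consent to study in eligible patients", with Go above 30%, Amend 15–30% and Stop below 15%. The Sample size section calls this the recruitment criterion. The measures of yield appear among the secondary outcomes: "Identification of patients at sites- Proportion of identified patients eligible for study inclusion- Participant recruitment uptake through recruitment strategies". No cut-off is attached to them.

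The Sample size section does plan a volume. With six practices, "nine young people would be expected to be eligible per month, and around 104 (the target eligible population size) over about 12 months", of whom 31 are expected to join. Under Statistical methods, the follow-up rate is total SBQ-R completions over three timepoints divided by a possible 93. The Discussion says that the progression criteria will determine whether a main trial is justified.

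**The concern.** Consent among eligible patients is conditional on their having been found. It shows how willing identified patients are, not how many a practice can supply. Under the Recruitment section the denominator can shrink at several points. In the records route, a clinician removes patients before anyone is invited. In the poster and opportunistic routes, patients first express interest, are then assessed for eligibility, and only then are asked to consent. Patients entering that way are few by selection and likely to say yes.

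The row that the protocol uses as its test of recruitment can therefore read Go whatever the yield. Yield per practice decides how many practices, and how long, a main trial would need. The study collects that figure but sets no level at which it would change the decision.

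**Working it through.** **Inputs.** Sample size section: incidence quoted as 60 per 10,000 person-years, then used as 60 per 1,000; half eligible; two-thirds of those identified; 900 patients aged 16–25 per practice; six practices; about 12 months; 104 eligible; 31 recruited. Table 1: the cut-offs. Statistical methods: follow-up denominator 93.

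**1. The plan's own chain.**
- Eligible per practice per year: 900 × 0.060 × 1/2 × 2/3 = 18, or 1.5 per month.
- Six practices: 9 per month, so 104 takes 104/9 = 11.6 months. This reproduces the plan.
- 30% of 104 = 31.2, the planned 31. (31/104 is 29.8%, just inside Amend. That is a separate point.)
- Implied recruitment rate: 31/(6 × 12) = 31/72 = 0.43 per practice-month.

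No row of Table 1 tests the 1.5 or the 0.43.

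**2. The recruitment row at low yield.** Suppose six practices find 40 eligible patients in 12 months and 13 consent.
- Consent: 13/40 = 32.5%, Go.
- Volume: 13/31 = 42% of plan; 13/72 = 0.18 per practice-month.

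**3. The other rows in the same case.** With 13 recruits, 12/13 willing to be randomised (92%) is Go, as is 9/13 (69%) for fidelity and for adherence. Follow-up depends on the denominator:

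| Denominator | Best possible with 13 recruits | Example: 32 completions |
|---|---|---|
| 3 × recruited = 39 | 39/39 = 100% | 32/39 = 82%, Go |
| Fixed at 93 | 39/93 = 41.9%, Stop | 32/93 = 34%, Stop |

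With 93 fixed, Go needs at least 25 recruits (75/93 = 80.6%; 24 recruits give at most 72/93 = 77.4%). Fifteen or fewer must be Stop (45/93 = 48.4%).

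**4. Reaching 31 by stretching the study.** Suppose twelve practices are needed for 12 months and 31 of 100 eligible patients consent.
- Consent 31%; willingness 27/31 = 87%; fidelity and adherence 21/31 = 68% each; follow-up 75/93 = 80.6%. All are Go on either denominator.
- Yield: 31/144 = 0.22 per practice-month, half of plan.

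The two qualitative rows contain no count and can read Go in any of these cases.

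**5. Is a shortfall plausible?** The quoted 60 per 10,000 is 6 per 1,000, not 60 per 1,000. At 6 per 1,000 the chain gives 900 × 0.006 × 1/2 × 2/3 = 1.8 eligible per practice per year. Six practices give 10.8, of whom 30% is about 3 recruits (0.045 per practice-month). The 12-month look-back in the eligibility criteria may add an initial batch of earlier cases.

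**6. Where to set Go.** Treat the count over 72 practice-months as Poisson with mean 31 (an assumption).
- Go at the expected value, 0.43: P(30 or fewer) = 48%. A study exactly on plan would miss Go almost half the time.
- Go at about 75% of plan, 0.75 × 31/72 = 0.32, which is 24 or more recruits: P(23 or fewer) = 8%.
- Stop below 50% of plan, 0.5 × 31/72 = 0.22, which is 15 or fewer: P = 0.1%.

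Variation between practices would widen these probabilities.

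**The case against.** - **The follow-up row would catch a large shortfall.** Read literally, the denominator of 93 makes follow-up Stop at 15 or fewer recruits and keeps it below Go under 25. A reader might infer that the study can score Go on every row after failing to recruit. On the written denominator that is not so for large shortfalls. However, 93 is 31 × 3 and may be only the planned figure. Held fixed, it reports a recruitment failure as a retention failure, and it does not detect 31 reached with extra practices or time.
- **The decision is not mechanical.** The Outcomes section says that the process will include Table 1, considered with the steering committee, the PPI group and the research team. The secondary outcomes are prespecified and would be visible. This reduces the concern. Volume is still left to judgement after the data are seen, while consent, fidelity, adherence and follow-up have fixed cut-offs.
- **Percentages come with 95% intervals.** That guards against very small samples, but not against this example: the exact interval for 13/40 is 18.6–49.1%, clear of the 15% Stop line.
- **Recruitment is one of three areas, and its specific objective is consent and willingness to be randomised.** True: Table 1 matches that objective, and it would be too strong to call recruitment the one uncertainty that the study exists to resolve. But the abstract lists recruitment rates first among the feasibility outcomes.
- **Low yield can be met with more practices.** Also true, which makes it partly a planning parameter. An Amend band is the natural place to record that.

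**Conclusion.** The concern holds in a limited form. Table 1 tests willingness among patients already found and does not test how many are found or recruited. The recruitment row can read Go at 42% of planned volume. All rows can read Go at half the planned yield if the study is extended to reach 31. At lower volumes, whether all rows can read Go depends on the follow-up denominator, which the protocol gives as 93 without saying what happens if fewer than 31 join.

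The documents do not support the inference that a study that recruits poorly would automatically proceed. A fixed 93 would give Stop on follow-up at 15 or fewer recruits, and the committee also sees the secondary outcomes. The gap is that no level of yield is fixed in advance for an area that the protocol itself calls untested. The worked cases are illustrations, not forecasts, and the 0.43 benchmark is only as sound as the incidence figure behind it.

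**What to change.** 1. Reconcile the incidence in the Sample size section (60 per 10,000 against 60 per 1,000) and restate the expected yield per practice. Any volume threshold depends on this.
2. Add a Table 1 row, agreed with the steering committee, for participants recruited per practice-month. Report eligible patients identified per practice-month beside it. Set Go below the expected value so that a study running to plan usually passes. If 0.43 stands, an example is Go at or above 0.32 (about 75% of plan), Amend 0.22–0.32 (50–75%), and Stop below 0.22. If the expected yield changes, rescale the bands.
3. Define practice-months as practices open multiplied by months open, so that added sites or time do not hide a low yield.
4. State the follow-up denominator as three times the number actually recruited, so that poor recruitment is not scored as poor retention.

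The cost is one table row and two clarifications. The counts are already needed for the secondary outcomes. The downside is one more criterion on which the study can miss Go, and the bands are a judgement for the committee.

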### Participant timeline

The schedule of study events is listed in
Table 2.

**Table 2. T2:** Schedule of study events.

Schedule of events		Enrolment	Baseline data collection	COPING delivery		Follow-up		
		0 weeks	0 weeks	T1	T2	8 weeks	4 months	6 months
Enrolment								
	Eligibility screen	✓						
	Informed consent	✓						
Participant descriptors								
Demographics	DOB, sex, gender		✓					
Language	Main language		✓					
Ethnicity	Ethnic origin		✓					
Education status	Type		✓					
Employment status			✓					
Internet use and access	Frequency and method		✓					
Medications								
Prescribed medications	Medication name, dosage, and frequency		✓					
Clinical outcomes								
Past self-harm	Method, timing of last self-harm, and frequency of episodes		✓					
Mood and suicidal or self-harm thoughts	PHQ-9		*✓*			✓	✓	✓
Attempted suicide	SBQ-R		✓			✓	✓	✓
COPING delivery								
Duration	Length of consultations (minutes)			✓	✓			
Deciding skills				✓	✓			
Goal setting				✓	✓			
Provision of COPING diary				✓				
Attendance at 2 ^nd^ COPING consult					✓			
Review of diary					✓			
Interviews								
Adverse events								
Recording of adverse events	Classifying and logging adverse events							

T
_1_ – first COPING consult, T
_2_ – second COPING consult

### Sample size

Non-randomised COPING delivery:

We will aim to recruit approximately six general practice sites and around 3 GPs at each site. The incidence rate of recorded self-harm in young people in general practice is around 60 per 10,000 person-years
^
23
^. This equates to 60 per 1,000 for the 16–25 age group over one year. If half are eligible for the study (30 per 1,000) and two-thirds of those are identified by our recruiting methods (20 per 1,000) then in a typical GP practice (assumed 6,000 registered patients of which 900 (15%) are in the 16–25 age group) about 18 eligible young people will contact their GP practice per year after self-harm (1.5 eligible young people per practice per month). If six practices are recruited to take part, nine young people would be expected to be eligible per month, and around 104 (the target eligible population size) over about 12 months. From this number (n=104) we would expect to recruit 31 participants (30%) (fulfilling the Go signal for progression for the recruitment criterion – see
Table 1) into the study.

The sample size of n=31 participants is required to test against the feasibility progression criteria (specifically the cut-off for a STOP signal) with at least 90% power, using the normal approximation method for binary outcomes using a 1-sample 1-sided test with 5% alpha (type I error) using the approach of Lewis
*et al.*
^
24
^ In line with the recommendation of the CONSORT-extension for randomised pilot and feasibility studies this provides necessary justification for the sample size requirement for the evaluation of the progression criteria for this feasibility study
^
25
^.

GP survey:

A sample of 100 GPs across England will be surveyed to elicit GP views about a future main RCT of COPING. Achieving 100 GP responses from a convenience sample has recently been shown to be achievable
^
26
^. If we expect 50% to respond then n=50 would be sufficient to provide a margin of error no greater than 0.1 standard error (SE) around an estimate for a proportion based on a binary response item “e.g., would you be willing to participate in a future RCT of COPING (yes/no)”. Therefore, if 25/50 respond ‘yes’, it will generate an estimate of the proportion who answer positively of 0.5 (50%) with margin of error <= +/-0.1 relating to a z-value of +/-1.282 allowing a 90% 1-sided confidence interval (CI) and 80% 2-sided CI (providing sufficiently precise confidence interval estimation) around the observed estimate.

Nested qualitative study:

It is anticipated that a sample of around 16–20 participants (8–10 young people participants and 8–10 GPs) is likely enough to identify problems in COPING delivery and achieve data saturation, where data no longer offers new insights
^
27
^.

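### The recruitment forecast counts only new presentations, although the 12-month eligibility window and the register search also admit patients who self-harmed before the site opened

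*Protocol article*

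**What the plan says.** The forecast is in the Sample size section, under non-randomised COPING delivery. It starts from an incidence ("The incidence rate of recorded self-harm in young people in general practice is around 60 per 10,000 person-years"), which it restates as a yearly rate ("This equates to 60 per 1,000 for the 16–25 age group over one year"). It then applies two fractions ("If half are eligible for the study (30 per 1,000) and two-thirds of those are identified by our recruiting methods (20 per 1,000") and a practice size ("assumed 6,000 registered patients of which 900 (15%) are in the 16–25 age group"). The result is that "about 18 eligible young people will contact their GP practice per year after self-harm (1.5 eligible young people per practice per month"). Over six practices, "nine young people would be expected to be eligible per month, and around 104 (the target eligible population size) over about 12 months", of whom 31 (30%) are expected to join.

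Two other sections define who can actually enter. Under Eligibility criteria, patients qualify if they are 16–25 and "have self-harmed (according to the definition of the National Institute for Health and Care Excellence) in the last 12 months". Under Recruitment, the first of three strategies works from existing records: "practice database searches will be developed for sites to use to identify potentially eligible patients". The article does not give the date, frequency or look-back of that search.

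Table 1 sets the recruitment progression criterion as consent among eligible patients, a proportion. Uptake by recruitment strategy is a secondary outcome. Table 2 collects the timing of last self-harm at baseline.

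**The concern.** The forecast treats eligibility as a flow: a patient becomes eligible on contacting the practice after self-harm, at a steady monthly rate. The eligibility rule and the register search also bring in a stock, namely everyone whose self-harm falls in the 12 months before the site opens. A first search can only find episodes that are already recorded, so it draws mainly on this stock. The two-thirds fraction is said to cover the study's recruiting methods, which include the search, yet the number it multiplies is one year of new presentations.

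Recruitment is a headline feasibility outcome, and the article calls recruitment to self-harm trials in general practice untested. The stock at a practice can be harvested once, whereas the flow recurs. If the two are reported together, the reader cannot tell how much of the yield would continue month after month. Nor can the reader tell how many recruits were reached soon after self-harm, although the Abstract's rationale is early intervention by the GP.

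**Working it through.** **Inputs (all from the Sample size section).** Incidence 60 per 10,000 person-years, restated as 60 per 1,000 per year; eligible share 1/2; identified share 2/3; 900 patients aged 16–25 per practice; 6 practices; uptake 30%.

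**Step 1. Reproduce the plan's figures.** Eligible per practice-year = rate × 1/2 × 2/3 × 900.
- At 60 per 1,000: 0.060 × 1/2 × 2/3 × 900 = 18 per year, or 1.5 per month. Six practices give 9 per month and 108 per year. The figure of 104 is reached at 104 / 9 = 11.6 months, and 30% of 104 is 31.2. The steps after the conversion therefore reproduce.
- At 60 per 10,000, which is 6 per 1,000: 0.006 × 1/2 × 2/3 × 900 = 1.8 per year. Six practices give 10.8 per year, or 0.9 per month. The stated 18 does not follow from the cited incidence. Flow alone would need 104 / 0.9 = about 116 months to reach 104.

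**Step 2. Add the stock.** Assumptions: a constant rate, one person per recorded event, and the same 1/2 and 2/3 shares for stock as for flow. A 12-month window then holds one year of flow at site opening. Let s be the share of that stock the search reaches. Eligible in 12 months = annual flow × (1 + s).

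| s | at 60 per 1,000 | recruits at 30% | at 60 per 10,000 | recruits at 30% |
|---|---|---|---|---|
| 0 | 108 | 32.4 | 10.8 | 3.2 |
| 0.25 | 135 | 40.5 | 13.5 | 4.1 |
| 0.50 | 162 | 48.6 | 16.2 | 4.9 |
| 0.75 | 189 | 56.7 | 18.9 | 5.7 |
| 1 | 216 | 64.8 | 21.6 | 6.5 |

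On the plan's rate, a fully reached stock of 18 × 6 = 108 already exceeds the 104 target. A late search shrinks the stock but does not remove it: a first 12-month search at month 6 still reaches back 6 months before opening, or 6 × 9 = 54 patients.

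**Step 3. Effect on a monthly rate.** With the full stock, average eligible per practice-month over T months = (18 + 1.5T) / T.
- T = 12: 36 / 12 = 3.0
- T = 24: 54 / 24 = 2.25
- T = 36: 72 / 36 = 2.0
- Flow only: 1.5

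A 12-month rate carried to 24 months per site is too high by 3.0 / 2.25 = 1.33. Carried to a design that takes new cases only, it is too high by 3.0 / 1.5 = 2. These ratios do not depend on which incidence is used, because stock and flow scale together.

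**The case against.** A reader might infer that the observed recruitment rate will overstate what an RCT can sustain. The article does not support that. The Table 1 criterion is a consent proportion, in which stock patients enter both numerator and denominator. No recruits-per-month threshold is set, and nowhere does the article say that RCT accrual will be projected from a pooled monthly rate. An RCT with the same look-back and search would find the same kind of stock at each new site, and its design is not yet fixed. This part of the objection stands, and the point is limited accordingly.

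The size can also be challenged. A full stock on day one needs an early search covering 12 months at all six sites, which is not stated. The two-thirds share is for all three strategies together, whereas the search is the main route to the stock. People who present again after opening would be counted twice. Hence 108 for the stock and 216 for the total are upper figures. On the plan's 60 per 1,000, leaving out the stock makes the forecast cautious and does not threaten the target of 31. At the cited incidence, the stock would yield only about 3 recruits, so it could not fill the study by itself.

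Finally, uptake by strategy is already to be reported. That helps but does not separate old from new cases: a repeat search can find new ones, and a poster or consultation can bring in someone who self-harmed months before.

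**Conclusion.** The forecast and the recruitment plan describe different populations. The Sample size section counts new presentations only, while the eligibility window and register search also admit patients who self-harmed before site opening. On the plan's own inputs the omitted stock is up to about 108, as large as the whole 12-month flow, so the eligible total lies between 108 and 216. At the cited 60 per 10,000 it lies between 10.8 and 21.6. The tenfold conversion is the larger problem and acts in the opposite direction; adding the stock does not close the gap to 104.

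No bias in the consent proportion is shown. A pooled monthly rate may overstate later recruitment by about a third if carried to 24 months per site, and by up to twofold for an incident-only design. All of this assumes a constant rate, one person per event and equal shares for stock and flow, and the two ratios also assume that the full stock is reached. The change is worth making because it is cheap and clarifies what the study can say about recruitment; it does not decide whether the study can proceed.

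**What to change.** - Reconcile the two incidence rates in the Sample size section first. Then restate the forecast as stock at first search plus monthly flow, with the assumed search date and look-back.
- Report identified, eligible and consented numbers separately for last self-harm before, and on or after, site opening. Record dates serve for identified and eligible patients; the baseline item on timing of last self-harm serves for those who consent.
- In any projection of RCT accrual, use the new-case rate for the monthly figure and add the stock once per practice.

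The cost is a reworded paragraph and one extra split in a descriptive table, with no further patients and no new questionnaire item. The cells will be small with 31 participants, and the sustained rate may look less favourable.
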